### Ethical review

The study protocol was approved by the Ethics Committee of the Faculty of Arts and Sciences at the University of Zurich (approval number 18.6.5; date of approval June, 21st, 2018). The trial will be executed in compliance with the Helsinki Declaration.

### Randomisation and allocation concealment

To avoid spill-over effects within school classes, we will conduct a cluster-randomised controlled trial using school class as a randomisation unit. Due to the heterogeneity of students in the different secondary schools, we will use a separate randomisation list for each school (stratified randomisation). Furthermore, to approximate equality of sample sizes in the study groups, we will use block randomisation with computer generated randomly permuted blocks of 4 cases [29].

Junior scientists supervising the baseline assessment will be blinded to the group allocation of school classes. In addition, group allocation will not be revealed to participants until they had provided their informed consent, username, mobile phone number, and baseline data. Furthermore, the research assistants who perform the computer-assisted follow up assessments for primary and secondary outcomes will be blinded to the group allocation.

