## Background

Several biological, psychological, and social transitions that occur during adolescence are essential for a young person’s later-life trajectory [1, 2]. These transitions offer opportunities for them to gain skills to achieve greater autonomy from adults, build social connections with peers, develop a positive body image, and form a sense of identity. However, these transitions also facilitate exploration and risk taking at a stage when cognitive functions of the brain are not yet fully developed [3]. Shifts of emotional regulations and increased risky behaviours result in vulnerabilities for mental and substance use disorders, which constitute the biggest contributors to the health burden of 10- to 24-year-old individuals [4]. Substance use and the development of substance use disorders often first emerge during adolescence and co-occur with mental disorders [1]. The Swiss data of the Health Behaviour in School-aged Children (HBSC) study [5] showed noticeably increases in the lifetime prevalence of alcohol, tobacco and cannabis consumption over the age groups of 11-to-15-year-olds. The prevalence of regular cigarette smoking (weekly or daily) increased from 2% among 13-year old boys to 12% among 15-year-old boys and from 2% in 13-year old girls to 9% in 15-year old girls. The prevalence of binge drinking increased from 19% in 14-year old boys to 27% in 15-year old boys and from 14% in 14-year old girls to 23% in 15-year old girls.

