### Participants, setting and procedure

We will test the intervention in secondary school students aged between 14 and 16 (grades 8 and 9). In this age group the prevalence of experimental and regular use of alcohol, tobacco and cannabis is increasing noticeably [5]. However, only a minority has established problematic or disordered substance use [5, 27]. Furthermore, nearly all adolescents at this age are familiar with how to use mobile phones and typically use them on a daily basis. According to the latest representative survey on media use in adolescents in Switzerland, 98% of the adolescents aged 14 and 15 years own a mobile phone and 98% use a mobile phone daily or several times per week [20]. Secondary schools in the German speaking part of Switzerland will be invited to participate in the study by cooperating regional centres for addiction prevention.

Employees of the above-mentioned centres for addiction prevention will arrange information sessions with a duration of 60 min in participating secondary school classes during regular school lessons reserved for health education. These information sessions will be led by junior scientist from the Swiss Research Institute for Public Health and Addiction, who are experienced in the work with young people, the provision of preventive interventions and trained on the study and on the program to be delivered.

The parents of the secondary school students in participating classes will be informed at least 1 week in advance of this session. They will receive a letter including information about the study and the intervention program and the parents are asked to give written informed consent to their child’s participation in the study.

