### Assessments and outcomes

At baseline, demographic variables (age, sex, migration background), data on mobile phone use as well as characteristics of the schools (location, type of school) and school classes (level, size, number of students present) will be assessed.

Baseline- and follow-up assessments will includeProblem drinking in the preceding 30 days, assessed by the short form of the Alcohol Use Disorders Identification Test, the AUDIT-C [37]. This test comprises 3 items on (1) frequency of alcohol consumption, (2) quantity of alcohol consumption, and (3) binge drinking. Pictures will be used to illustrate the quantity of a standard drink, which corresponded to 12–14 g of pure alcohol. Based on a validation study of a large German sample, a cut-off of ≥5 will be used [38].30-days point prevalence rate for smoking abstinence (“not having smoked a puff” within the past 30 days according to the criteria of the Society for Nicotine and Tobacco Research [39]).Quantity of cigarettes smoked in the preceding 30 days by assessing the number of smoking days and the typical number of cigarettes smoked per smoking day.Cannabis use in the preceding 30 days assessed by an item of the HBSC study [5] addressing the number of cannabis consumption days.Perceived stress assessed by a four-item version [40] of the Perceived Stress Scale [41]. This scale measures the degree to which students appraised situations as stressful over the preceding month.Interpersonal competences, assessed by the brief version of the Interpersonal Competence Questionnaire [42], addressing the following domains of social competence: (1) initiation of relationships, (2) negative assertion, (3) disclosure of personal information, (4) emotional support, and (5) conflict management.

The primary outcomes of the planned study are (1) prevalence of problem drinking in the preceding 30 days according to the AUDIT-C and (2) prevalence of cigarette smoking in the preceding 30 days (having smoked at least a puff according to the criteria of the Society for Nictotine and Tobacco Research [39]).

Secondary outcomes arePrevalence of cannabis use in the preceding 30 days (having used cannabis at least once)Quantity of alcohol use in the preceding 30 daysQuantity of cigarettes smoked in the previous 30 daysFrequency of cannabis use in the preceding 30 daysPerceived stressInterpersonal competences

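### Grade (8 or 9) is neither balanced in the class randomisation nor fixed as a covariate, although the protocol's own data show binge drinking rising 8–9 points in a year: a small, avoidable loss of precision

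*Protocol article*

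**What the plan says.** Under Randomisation and allocation concealment the article states that "we will conduct a cluster-randomised controlled trial using school class as a randomisation unit", that "we will use a separate randomisation list for each school (stratified randomisation", and that "we will use block randomisation with computer generated randomly permuted blocks of 4 cases". The reason given for stratifying is that students differ between schools. No other balancing factor is named.

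The population spans two school years: "We will test the intervention in secondary school students aged between 14 and 16 (grades 8 and 9" (Participants, setting and procedure).

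The Background gives the age gradients. For binge drinking: "The prevalence of binge drinking increased from 19% in 14-year old boys to 27% in 15-year old boys". The corresponding figures for girls are 14% and 23%. For regular smoking, over two years, prevalence in boys "increased from 2% among 13-year old boys to 12% among 15-year-old boys"; in girls it went from 2% to 9%.

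Under Data analyses, the models contain study group, time and their interaction. Further baseline variables are added only if found necessary to deal with baseline differences. Age is recorded at baseline, but neither age nor grade is named as a covariate.

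**The concern.** The plan balances one source of heterogeneity, school, and leaves free another that it documents itself. Two classes in the same school but a year apart may differ in drinking by about as much as the intervention is expected to achieve. A school-level list with blocks of four can put both grade-9 classes of a four-class school in the same arm.

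What is at stake is precision. Chance differences in grade mix add noise to the arm comparison, and grade differences between classes may form part of the intra-cluster correlation that drives the design effect. The covariate rule does not reliably recover this, because it depends on what imbalance is seen and names no variable.

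**Working it through.** **1. The plan's own figures (Sample size calculation).** With an odds ratio of 0.60:
- Drinking: 25% in controls gives 16.67% under intervention, a difference of 8.3 points. The formula for two proportions (two-sided 5%, 80% power, no continuity correction) gives 372 per arm; the plan states 370.
- Smoking: 22% gives 14.47%, a difference of 7.5 points. The formula gives 413 per arm; the plan states 410.
- Design effect: 1 + (13 − 1) × 0.05 = 1.60; 410 × 1.60 = 656 per arm; 1312 in total; 1312/13 ≈ 101 classes.

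All of these reproduce to within rounding. With 656/1.60 = 410 effective participants per arm, power is 83.7% for drinking and 79.8% for smoking.

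**2. Grade gradients (Background).**
- Binge drinking, one year: boys 27 − 19 = 8 points; girls 23 − 14 = 9 points; mean 8.5.
- Regular smoking, two years: boys 12 − 2 = 10 points, about 5 per year; girls 9 − 2 = 7 points, about 3.5 per year.

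**3. Chance imbalance in grade.** Assumption: 25 schools, each with two grade-8 and two grade-9 classes. A block of four has C(4,2) = 6 equal splits. In 2 of the 6, both grade-9 classes share an arm; in the other 4, grade is balanced. The number of grade-9 classes in the intervention arm of one school is therefore 0, 1 or 2 with probabilities 1/6, 4/6 and 1/6, which has variance 1/3. Over 25 schools the SD of the total is √(25/3) = 2.89. Each arm has 50 classes, so the difference in grade-9 share has SD 2 × 2.89/50 = 0.115. The exact distribution gives an 11.7% chance of a difference of at least 20 points and 5.6% of more than 20.

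Simulations with 2 to 8 classes per school, grades mixed about half and half, gave SDs of 0.105 to 0.121. The result is therefore not sensitive to school size. It does depend on schools contributing both grades.

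**4. Effect on an unadjusted follow-up comparison of drinking.** SD: 0.115 × 8.5 ≈ 1.0 point, against a target of 8.3. A 20-point imbalance shifts the difference by 0.20 × 8.5 = 1.7 points, and a true odds ratio of 0.60 would then appear as about 0.54 or 0.67. For scale, the standard error of the difference is √[1.60 × (0.25 × 0.75 + 0.167 × 0.833)/656] ≈ 2.8 points.

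**5. Upper bound on the precision gain.** Suppose that the correlation of 0.05 includes grade variance and that grades are mixed half and half. Grade then accounts for 0.25 × d² / [p(1 − p)] of it, where d is the gap between grades. For p, both the control rate and the mean of the two arm rates were used; the ranges cover both.

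| Outcome | d (points) | Remaining ICC | Design effect | Power at 656 per arm |
|---|---|---|---|---|
| Drinking | 8 to 9 | 0.041 to 0.038 | 1.50 to 1.45 | 86.0% to 87.1% (from 83.7%) |
| Smoking | 3.5 to 5 | 0.048 to 0.046 | 1.58 to 1.55 | 80.3% to 81.1% (from 79.8%) |

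Example for drinking with d = 0.085 and mean rate 0.208: 0.25 × 0.085²/0.165 = 0.011; 0.05 − 0.011 = 0.039; 1 + 12 × 0.039 = 1.47. The standard error falls by 1 − √(1.47/1.60), about 4%. For the planned group-by-time contrast the gain is smaller still, put at 0 to 4%, because a stable grade difference cancels in the change from baseline.

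**The case against.** The strongest reply is that nothing here is wrong. Stratifying by school alone is a valid scheme and every stated figure reproduces. Four parts of the reply stand.

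- **No bias.** A reader might infer that arm and grade are confounded in the sense of systematic bias. The documents do not support that: the imbalance is chance. If grade variance is within the correlation of 0.05, the standard error already reflects it and 1312 already pays for it. If it is not within it, the ICC reduction in step 5 falls away.
- **The model helps.** The group-by-time contrast removes a grade difference that is constant over time. The 1-point shift applies only to an unadjusted follow-up comparison.
- **Smoking gains little.** A reader might apply the drinking gradient to smoking and expect about 3 points of power. The Background supports only 3.5 to 5 points a year for smoking, hence a gain of about 0.5 to 1.3. Smoking is the outcome that sets the sample size.
- **Inputs are assumed or extrapolated.** The number of schools and the grade mix are not stated. A school that enters one grade only is already balanced. The gradients describe ages 13 to 15 and related measures, not AUDIT-C ≥5 or any smoking 18 months later.

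A reader might also want class level balanced, since the plan records "school classes (level, size, number of students present". The documents give no outcome data by level, so that extension is unsupported.

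What does not stand is that the model makes the point moot. The interaction does not remove differing trajectories between grades, and a covariate rule that waits for observed imbalance does not guarantee that grade is used.

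**Conclusion.** The point holds as a minor design weakness. Grade is left to chance in the allocation and to discretion in the analysis, although the protocol documents a gradient for binge drinking about as large as its target effect. The cost is limited: a chance shift of about 1 point (SD) in an unadjusted drinking comparison, and at most 2 to 3 points of power for drinking and about 1 for smoking. These figures rest on schools contributing both grades in roughly equal numbers, on the gradient at ages 14 to 15 carrying over to follow-up, and, for the power gain, on the ICC of 0.05 including grade variance. The sample size of 1312 is not called into question.

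**What to change.** **Analysis (the main change).** In Data analyses, replace the conditional covariate rule, as far as grade is concerned, with a prespecified fixed term for grade, or baseline age, in the primary models, included whatever imbalance is observed. This recovers nearly all of the available gain at almost no cost.

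**Allocation.** In Randomisation and allocation concealment, where a school enters classes of both grades, allocate all its classes in one central draw, at random from the equal splits that also balance grade. This is preferable to separate school-by-grade lists with blocks of four. In the simulation with four classes per school, such lists left many blocks incomplete: the imbalance SD fell only to 0.08, and the SD of the arm difference in class numbers rose from 0 to about 8. Balancing class level, or grade across schools, is not needed.

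**Cost.** Classes and their grades must be listed when a school enrols. Balance stays inexact with odd or single classes per grade. Allocation within a pair of same-grade classes becomes more predictable once one is known, so the draw must stay concealed until baseline is complete in all classes of the school.

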## Methods/design

### Design and hypotheses

A two-arm cluster-randomised controlled trial will be conducted to test the efficacy of the *SmartCoach*, a mobile phone-based life-skills training program to prevent substance use among secondary school students. The efficacy of the intervention will be tested in comparison to an assessment only control group. The study participants will be assessed at baseline and at 6- and 18-months follow-up (Fig. 1). Our main hypothesis is that the individually tailored intervention program with a duration of 6 months will be more effective than assessment only, to prevent the onset and escalation of problematic alcohol and tobacco use at 18-months follow-up.

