Based on an estimated OR of 0.60 and an expected 30-days prevalence of tobacco smoking in 16 year-old adolescents of 22% in the control group at the 18-month follow-up (mean of prevalence in 15-year olds derived from HBSC study [5] and in 17-year olds derived from Addiction Monitoring [31]), a sample size of *n* = 410 in each study group would be required to have 80% power for a χ^2^-test (α = 5%, 2-sided) in order to detect this difference.

As secondary school students are nested within school classes, we additionally need to consider a potential design effect for the calculation of the sample size for our study. Based on [26, 32], an average cluster size of 13 study participants per school class and an intra-cluster correlation coefficient of 0.05 could be expected. This would result in a design effect of 1.60. Multiplying this design effect by the required size for an unnested sample (*n* = 410) results in a required sample size of *n* = 656 per study group and a total of *n* = 1312 study participants. Thus, based on the participation rates of the previous MobileCoach studies [32, 33] and the pre-post study on a mobile phone-based life- skills training, approximately 100 secondary school classes are required to reach this sample size.

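### School-specific lists with blocks of 4 classes leave two-class, six-class and single-class schools less well balanced than they could be; this costs some precision but causes no bias

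*Protocol article*

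**What the plan says.** The section Randomisation and allocation concealment of the protocol article fixes three things.

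- The trial is cluster-randomised, "using school class as a randomisation unit".
- Allocation is stratified by school. The reason given is "Due to the heterogeneity of students in the different secondary schools", and the consequence drawn is that "we will use a separate randomisation list for each school (stratified randomisation").
- Within each list, "to approximate equality of sample sizes in the study groups", the plan uses "block randomisation with computer generated randomly permuted blocks of 4 cases".

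Read together, the cases in a block are classes of one school. The section gives no rule for a school whose classes do not fill a block.

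The section Sample size calculation states that "an average cluster size of 13 study participants per school class and an intra-cluster correlation coefficient of 0.05 could be expected" and that "approximately 100 secondary school classes are required to reach this sample size". Neither the number of schools nor the number of classes per school appears anywhere in the article.

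**The concern.** Stratifying by school is meant to place both arms inside each school, so that school differences cancel from the comparison. Blocking delivers this only where blocks are filled or where the part used is forced to be near balance. A block of 4 achieves that after three or four classes. It does not after two, because the first two positions may hold the same arm. Nor does it balance single-class schools against one another, because each opens its own list and uses only its first position.

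A two-class school that falls wholly into one arm gives no within-school comparison, and its school effect enters the treatment contrast. Precision that the stratification could have supplied is then given up, and the arms can drift apart in number of classes.

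**Working it through.** **1. The plan's own figures.** The design effect is 1 + (13 − 1) × 0.05 = 1.60. Then 410 × 1.60 = 656 per group, 1312 in total, and 1312 / 13 = 100.9 classes. These agree with the article. The calculation uses the class-level correlation only and makes no reduction for stratification.

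**2. Balance within a school.** There are six orderings of two intervention and two control places. Cutting the list off after k classes gives:

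| Classes in school | Chance of a single-arm school, blocks of 4 | Same, simple randomisation | Split under blocks of 4 |
|---|---|---|---|
| 1 | 100% | 100% | 1:0, independent across schools |
| 2 | 2/6 = 33.3% | 50% | 1:1 in 2/3, 2:0 in 1/3 |
| 3 | 0 | 25% | always 2:1 |
| 4 | 0 | 12.5% | always 2:2 |
| 5 | 0 | 6.25% | always 3:2 |
| 6 | 0 | 3.1% | 3:3 in 2/3, 4:2 in 1/3 |

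With 3, 4 or 5 classes the split is already as even as it can be. How many two-class schools will join is not stated. If there were 10, 20, 30 or 50, then 3.3, 6.7, 10 or 16.7 of them would be expected in one arm only.

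**3. Precision in the extreme case.** Assume 50 schools of two classes, 13 students per class and total outcome variance 1. Of the correlation of 0.05, let s lie between schools. The article gives no such split, so s = 0.02 to 0.04 is an assumption.

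- Variance of a class mean: 0.05 + 0.95/13 = 0.1231.
- Part not due to school: w = 0.1231 − s, which is 0.1031 or 0.0831.
- Variance implied by the sample size calculation: 2 × 0.1231 / 50 = 0.00492.
- Even split in every school: 2w / 50 = 0.00412 or 0.00332.
- Blocks of 4, school not modelled: the mean squared class imbalance per school is 4 × 1/3 = 4/3, so the variance is about (2w + 4s/3) / 50 = 0.00466 or 0.00439.
- Blocks of 4, school modelled: split schools give information 1/(2w) each. Single-arm schools contribute only through the between-school comparison. The variance is about 1 / {50 × [1/(3w) + 1/(6w + 12s)]} = 0.00455 or 0.00397.

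These closed forms ignore chance inequality in arm size. Simulated allocations, which include it, give:

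| | s = 0.02 | s = 0.04 |
|---|---|---|
| Excess over even split, school modelled | 11% | 20% |
| Excess over even split, school not modelled | about 14% | about 32% |
| Relative to planned variance, school modelled | 7% lower | 19% lower |
| Relative to planned variance, school not modelled | 5% lower | 11% lower |

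With s = 0.01 the excess over an even split is about 6%. If every school had six classes, and s ran from 0.01 to 0.04, it would be 1–3% (school modelled) or 2–10% (not modelled).

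**4. Arm sizes.** In the all-two-class case the larger arm holds 58 of 100 classes at the 95th percentile. That alone raises the variance by 1/(4 × 0.58 × 0.42) − 1 = 2.6%.

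**The case against.** The strongest reply is that the plan never relied on the precision in question. The sample size rests on the full class-level design effect. Even if every school supplied two classes, the expected variance would stay 5–19% below the planned one. A reader might convert the 11–20% excess into a loss of 1 − 1/1.11 = 10% to 1 − 1/1.20 = 17% of the sample and infer that the trial is underpowered. The documents do not support that: the comparison is with an ideal even split, not with the planned variance. This part of the reply stands in full.

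A reader might also infer that the block size cancels the stratification. It does not. Two of three two-class schools are still split, against one of two under simple randomisation, and every school with three or more classes contains both arms.

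Three further points have weight. No document says that two-class schools are common, so the figures describe an extreme. Allocation remains random, and the protocol claims only approximately equal groups, so neither bias nor contradiction follows. Baseline measurements of the outcomes and the optional covariates in Data analyses may absorb some stable school differences, which the calculation above ignores. In the other direction, the nesting levels that section offers as examples do not include school; if school is left out of the model, the larger figures are the relevant ones.

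What does not stand is the suggestion that this is merely detail left to a fuller document. The article itself fixes the unit, the lists and the block size, and that combination fits its stated purpose poorly for some school sizes.

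**Conclusion.** The point holds as a limited one. In schools with two classes the intended balance fails with probability 1/3, in six-class schools it is imperfect with probability 1/3, and single-class schools are not balanced against each other at all. With 3, 4 or 5 classes nothing is lost.

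The size depends on classes per school, which are not given, and on the between-school share of the correlation, which is assumed. The upper figures of 20% (school modelled) and 32% (not modelled) need both an all-two-class trial and a between-school share of 0.04; if most schools supply three to five classes, the effect is negligible. In every case it is forgone precision, with the comparison unbiased and the stated sample size intact. It merits a change because the remedy is nearly free.

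**What to change.** Before any session in a school, randomise all its participating classes in one draw and split them as evenly as possible, with the arm of an odd class chosen at random. Place single-class schools together on one common blocked list. State the expected number of classes per school.

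Do not replace the blocks of 4 by blocks of 2 used one class at a time: once the first class is allocated, the second would be predictable, which would weaken the concealment that the protocol sets out.

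The cost is a change to the randomisation program before the first school enters, with no extra participants. The one practical demand is that a school's participating classes be known before its draw.
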